## Abstract

**Background:** Despite intravenous thrombolysis and endovascular therapy for acute ischemic stroke (AIS), many survivors still have varying degrees of disability. Glyceryl trinitrate (GTN), a nitric oxide (NO) donor, has been previously reported to induce neuroprotection after AIS. The use of GTN to reduce brain damage after stroke remains yet to be elucidated. This study was designed to explore the safety, feasibility, and preliminary efficacy of intravenous administration of GTN after AIS.

**Methods:** A prospective randomized controlled trial is proposed with AIS patients. Participants will be randomly allocated to GTN group and control group with a 1:1 ratio (*n* = 40). Both groups will be treated with standard therapies according to the current stroke guidelines. Participants allocated to the GTN group will receive intravenous administration of GTN (5 mg GTN in 50 ml saline at a rate of 0.4 mg/h that is continued for 12.5 h/day for 2 days) within 24 h of symptom onset. Participants allocated to the control group will receive intravenous administration at equal capacity of 0.9% normal saline (NS) (total 50 ml/day at 4 ml/h that is continued for 12.5 h/day for 2 days). The primary outcome is safety [systolic blood pressure (SBP) <110 mmHg, headache], while the secondary outcomes include changes in functional outcome and infarction volume.

**Discussion:** Rapid Intravenous Glyceryl Trinitrate in Ischemic Damage (RIGID) is a prospective randomized controlled trial that aims to ascertain the safety, feasibility, and preliminary efficacy of intravenous GTN as a neuroprotection strategy after AIS. These results will provide parameters for future studies as well as provide insights into treatment effects. Any possible neuroprotective qualities of GTN in AIS will also be elucidated.

**Trial Registration:**www.chictr.org.cn, identifier: ChiCTR2100046271.

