### Interventions

Participants in both groups will be treated with the standard management according to the guidelines (30). In order to ensure the stability of administration speed and the stability of BP, patients allocated to the GTN group will undergo intravenous administration of GTN (5 mg GTN in 50 ml saline, with a speed of GTN 0.4 mg/h continued for 12.5 h/day, for 2 days) within 24 h of symptom onset. In the control group, 0.9% NS will be administered by continuous intravenous pumping with a speed of 4 ml/h continued for 12.5 h/day, for 2 days. Since no standard intravenous dose of GTN is available for AIS, the doses and administration of intravenous GTN are determined by following considerations. First, according to routine dosage of intravenous GTN, 0.3 mg/h (up to 20 mg/h) is applied. Second, because of the dose-dependent reductions in SBP (31) by GTN, we will use the similar low dose at 0.4 mg/h for 12.5 h/day to prevent excessive reduction of systemic BP for safety purposes. In addition, compared with intravenous administration, studies (20, 21, 25, 32) have shown that transdermal GTN patches (at a 0.4 mg/h rate for 12.5 h during a single application), in which there are about 75% of nitroglycerin systemically bioavailable after administration (33), reduce SBP by 5.8–13 mmHg after AIS that is within the range in the present study. Vital signs (i.e., BP, heart rate, body temperature, respiratory rate of the patients) and possible adverse drug reactions such as hypotension and headache, will be closely monitored during the whole treatment period. If the patients show a tendency to develop adverse reactions and complications, the trial shall be immediately stopped, and routine treatment shall be given.

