### Outcomes

#### Primary Outcomes (Safety Assessment)

The primary safety outcome is SBP <110 mmHg. The primary outcome SBP <110 mmHg was defined as average SBP <110 mmHg within 24 h after GTN has been started. BP will be measured every 15 min between 0 and 2 h after GTN is started, every 30 min between 2 and 12 h, every 120 min between 12 and 48 h, and twice a day after 48 h. The target levels of BP poststroke remain unclear within the available literature (34–37). The current AIS guidelines differentiate BP targets based on a variety of factors including whether the patient receives alteplase, undergoes mechanical embolectomy, and/or experiences a hemorrhagic conversion. Prior studies (34–37) found a U-shaped relation of BP with functional outcome: both low BP and high BP were associated with poor outcome. There is no clearly defined cutoff for low BP in patients with AIS. Previously identified nadirs such as the tipping point in the U-shaped association between BP and outcome also vary between 120 and 180 mmHg (34, 36). Because of this variability, according to prior studies, we will use the lowest 10th percentile as a cutoff, low SBP, namely, SBP <110 mmHg.

The secondary safety outcomes are headache. Headaches related to GTN were defined as follows: GTN responders are those who develop a mild to moderate headache (headache scores 3–6) within 5–15 min with a short-lasting duration (maximum of 30 min) and spontaneously recover within 1 h after administration of GTN without the need for any rescue medication (38). In addition, severe headaches (scores 7–10) or the use of analgesia for GTN-caused headaches will be accounted for as secondary safety outcomes. If patients experience severe headaches, vital signs (i.e., BP, heart rate, body temperature, respiratory rate of the patients) will be closely monitored, and a CT scan will be obtained to analyze the cause of the headache.

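### The headache outcome, as defined, leaves out untreated mild-to-moderate headaches that start after 15 min or last over 30 min during a 12.5 h/day infusion

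*Protocol article*

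**What the plan says.** The outcomes section of the protocol article, under Primary Outcomes (Safety Assessment), states that "The secondary safety outcomes are headache". It then defines a GTN-related headache by intensity and onset: "GTN responders are those who develop a mild to moderate headache (headache scores 3–6) within 5–15 min". The same sentence also requires a brief, untreated course: "with a short-lasting duration (maximum of 30 min) and spontaneously recover within 1 h after administration of GTN without the need for any rescue medication". It adds one further group: "severe headaches (scores 7–10) or the use of analgesia for GTN-caused headaches will be accounted for as secondary safety outcomes". No other headache is named as counting.

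The Interventions section sets the exposure. GTN is infused "with a speed of GTN 0.4 mg/h continued for 12.5 h/day, for 2 days" and saline "with a speed of 4 ml/h continued for 12.5 h/day, for 2 days". The same section says that headache is monitored as a possible adverse reaction throughout treatment. The Statistical Analyses section says that adverse-event frequencies will be tabulated and compared between arms. Neither section says how a headache is counted.

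The Abstract gives headache a different status: "The primary outcome is safety [systolic blood pressure (SBP) <110 mmHg, headache".

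**The concern.** The definition describes a brief headache shortly after dosing that resolves by itself, but the drug is given continuously for half a day on each of two days. A headache of the same intensity that begins later, or that persists, meets no criterion unless it becomes severe or is treated. The briefer event counts and the longer one does not, which is the wrong way round for a tolerability outcome.

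The analgesia criterion adds a problem of comparability. It applies only to headaches caused by GTN. The Randomization and Blindness section masks patients and assessors, so assessors cannot establish that cause, and a saline patient's headache cannot truly have it. Headache is one of only two named safety outcomes in a phase 1 safety study of 40 patients. A few uncounted or unevenly counted events could change how tolerability is read.

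**Working it through.** **Inputs, all from the article.** GTN 5 mg in 50 ml at 0.4 mg/h, and saline 50 ml at 4 ml/h (Study Design, Interventions). Score, onset, duration and recovery limits (Primary Outcomes). Two arms from 40 patients at 1:1, so 20 per arm (Randomization and Blindness, Estimation of Sample Size). The article gives no headache rate, onset time or duration, so there is no headache figure to reproduce.

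**Step 1: exposure.** 5 mg ÷ 0.4 mg/h = 12.5 h, and 50 ml ÷ 4 ml/h = 12.5 h. The stated duration reproduces in both arms. 12.5 × 60 = 750 min per day.

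**Step 2: onset window.** 15 − 5 = 10 min, and 10 ÷ 750 = 1.3% of each infusion. The window closes at 15 ÷ 750 = 2%. In the remaining 750 − 15 = 735 min (98%), a new untreated score 3–6 headache cannot qualify. If the clock starts only with the first infusion, the window closes at 15 ÷ 1,500 = 1% of the total infusion time.

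**Step 3: apply the criteria to hypothetical cases.**
- Score 5, starts at minute 10, gone within 30 min, untreated: counts.
- Score 5, starts at minute 40, untreated: onset too late, not severe, no analgesia. Not counted.
- Score 5, starts at minute 10, lasts 2 h, untreated: too long, not severe, no analgesia. Not counted.
- Score 5, starts at minute 40, analgesic given: counts only if attributed to GTN. Read literally, it does not count in a saline patient.
- Score 8, any time, either arm: counts, with no attribution needed.

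**Step 4: related wording.** A GTN-related headache is defined as one that needs no rescue medication, yet "the use of analgesia for GTN-caused headaches will be accounted for as secondary safety outcomes". The article therefore has no definition of a GTN-caused headache that is treated. Nor does it say whether the time limits run from the start or the end of the infusion, or restart on day 2.

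**Step 5: possible effect on the comparison (illustration only).** Assume true headache rates of 50% on GTN and 10% on saline, and that the same fraction q of headaches meets the definition in each arm. With n = 20 per arm, two-sided 5%, p1 = 0.5q, p2 = 0.1q and p̄ their mean, the normal approximation is

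power = Φ{[(p1 − p2) − 1.96·√(2p̄(1 − p̄)/n)] / √([p1(1 − p1) + p2(1 − p2)]/n)}.

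- q = 1: 0.50 v 0.10, power about 81%
- q = 0.5: 0.25 v 0.05, about 42%
- q = 0.25: 0.125 v 0.025, about 22%
- q = 0.1: 0.05 v 0.01, about 11%

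The approximation is rough at such small counts. It shows the direction of the effect, not its size in this trial.

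**The case against.** The best defence is that these headaches are not lost to the trial. Headache is monitored throughout treatment, adverse events are tabulated, and the rule for moving to phase 2 refers to adverse reactions in general. This stands in part. A reader might infer that late or prolonged headaches are never counted anywhere, or that the phase 2 decision rests on the narrow definition; the article says neither. But the sections that could catch these headaches set no counting rule, and the only definition of a GTN-related headache excludes them.

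A second defence is that the responder wording describes a subtype, and nothing says that other headaches are discarded. It is true that no sentence discards them. Even so, the article lists what counts and these headaches are not on the list.

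Three further limits stand in full:
- **Time share.** A reader might take 1.3% to mean that almost all headaches are missed. That would require onset to be spread evenly over the infusion, for which the article offers nothing. Nor does it show that late or prolonged headache is the expected pattern.
- **Attribution.** The condition on GTN as cause naturally attaches to analgesia only. A reader might extend it to severe headache, but the sentence does not require that. The timing and score limits can also be applied from the start of infusion in either arm.
- **Status.** The Abstract may simply compress a section whose heading is primary but whose text ranks headache second. The mismatch is minor.

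Leaving detail to a fuller document is no answer here, because the article states a definition and that definition produces the gap.

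**Conclusion.** The point holds for the headache outcome as written. An untreated score 3–6 headache that starts after 15 min or lasts more than 30 min meets no counting criterion, although the infusion lasts 750 min on each of two days. Treated headaches below severe depend on an attribution that masked assessors cannot establish and that is not like-for-like between arms. Severe headache is unaffected.

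The conclusion rests on reading the listed criteria as the whole outcome. The number of events missed cannot be estimated from the article, and the power figures depend on assumed rates. The definition should be corrected. The point is not critical, because the Methods make headache a secondary safety outcome in a 40-patient pilot and the sample size is based on blood pressure.

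**What to change.** - Count, in both arms and regardless of cause, any new or worsened headache scoring 3 or more from the start of the first infusion to the end of the 2-day treatment period, for example 48 h.
- Record maximum score (3–6 or 7–10), onset time, duration and any analgesic use, with times measured from the start of each infusion.
- Delete attribution to GTN as a condition for counting.
- Keep the responder pattern as a descriptive subtype, applied in the same way in both arms.
- Give headache the same status in the Abstract and in the outcomes section.

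The cost is a change of outcome wording and a line on the case report form. Blood pressure is already measured on a fixed schedule to 48 h, so headache can be recorded at the same times. The downside is higher headache counts that include background headache in both arms; the control arm shows how large that background is. Dose and clinical care are not affected.

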#### Secondary Outcomes (Efficacy Assessment)

The primary efficacy outcome is the mRS at 90 days (mRS scores of 0–2 indicate functional independence). Secondary efficacy outcomes include the rate of the 0–2 mRS at 90 days, the incidence of death at 90 days, blood nitrate index detection at 1 day [cyclic guanosine monophosphate (cGMP, second messenger to NO), L-arginine (substrate for NO), and L-citrulline (co-product with NO)], infarct volume, as well as NIHSS scores at days 1, 7, 14, 30, and 90. The mRS and NIHSS scores will be obtained by a blinded personnel to the research. Face-to-face encounters in the consultation room will be used in the study to calculate mRS and NIHSS. Brain infarct volume will be determined by MRI diffusion-weighted imaging technique. The lesion profile plotted at each individual level by an image tool [region of interest (ROI)] on the workstation will be used to calculate the area. The levels will be multiplied by the thickness of each level and summed to calculate the infarct volume. The calculations will be performed by personnel blinded to clinical data and randomization at baseline and at day 7 ± 1.

Patients diagnosed as AIS without corresponding lesions on MRI are rare (<2%) in our stroke center. Patients who are misdiagnosed with stroke through negative MRI will be reported, and subgroup analysis will be performed.

### Estimation of Sample Size

There are no data available for reference because no completed clinical study of intravenous GTN in AIS patients currently exists. However, Hertzog (39) has suggested that 10–20 patients in each group are sufficient to assess the feasibility of a pilot study, while Dobkin (40) has shown that 15 patients in each group is usually enough to decide whether a larger multicenter trial should be conducted. In order to determine the sample size for each group, a power analysis was conducted based on the work of a prior study (20) that GTN can make a difference of 10 mmHg in SBP as compared to placebo groups. For the difference in BP at 10 mmHg, standard deviation at 10 mmHg, in order to have alpha exceed 95%, and beta = 0.8, a sample size of 16 patients per group has been calculated. As we expect to include around 20% for treatment dropouts and crossovers and for losses to follow-up, we will increase this sample size with 20% and aim to recruit 40 patients. The results of this study should be able to determine the initial safety and feasibility of intravenous infusion of GTN in AIS patients. The data will be used to estimate sample size and conduct a power calculation to plan a phase 2 trial for efficacy.

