### Statistical Analyses

All analyses are based on the intention-to-treat (ITT) principle, including all randomly enrolled subjects. Compared to the control group, if the GTN group did not have an increase in the incidence of adverse reactions and there was no difference in 90-day prognosis between the two groups, we would move forward with a phase 2 trial.

Categorical variables including the proportion of good functional outcomes and the frequency of adverse events will be presented as counts and percentages. χ^2^ test, Fisher exact test, or continuity correction will be used where appropriate for comparison between the two groups. If the continuous variables including NIHSS score and infarct volume conform to the normal distribution, results shall be indicated by mean ± standard deviation and tested by *t*-test, and if they do not conform to the normal distribution, results shall be indicated by median and interquartile range and tested by Mann–Whitney *U*-test. p < 0.05 will be considered statistically significant. SPSS 22.0 software (IBM Inc., Armonk, NY) will be used for statistical analysis.

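### The only power figure is for mean SBP, which is not a declared outcome; the binary primary outcome has no power or precision statement, and the error terms are mislabelled

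*Protocol article*

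**What the plan says.** Under Primary Outcomes (Safety Assessment): "The primary safety outcome is SBP <110 mmHg". The same paragraph defines this as the average SBP over the 24 hours after GTN is started, so each patient is a yes or a no. The threshold is described as a lowest 10th percentile taken from prior studies. No expected rate is given for either arm of this trial.

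Under Estimation of Sample Size, the section first cites two pilot-size recommendations (10–20 and 15 patients per group). It then reports a power analysis based on a prior study in which "GTN can make a difference of 10 mmHg in SBP as compared to placebo groups". The inputs are: "For the difference in BP at 10 mmHg, standard deviation at 10 mmHg, in order to have alpha exceed 95%, and beta = 0.8". The result is 16 per group, raised for about 20% losses to 40 in total. The section concludes: "The results of this study should be able to determine the initial safety and feasibility".

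Under Statistical Analyses: "Categorical variables including the proportion of good functional outcomes and the frequency of adverse events will be presented as counts and percentages". These are compared by chi-square, Fisher's exact or continuity-corrected tests, and "p < 0.05 will be considered statistically significant". Mean SBP does not appear in either outcome section.

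**The concern.** A calculation that uses a difference in mmHg and an SD is for comparing two means. The primary outcome compares two proportions. The one formal power figure therefore belongs to a comparison that the article does not declare, and the outcome it does declare has neither a power nor a precision statement.

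The wording of the error terms is a second fault. As normally defined, beta is the type II error, so a beta of 0.8 means 20% power, and an alpha above 95% is not a usable significance level.

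What is at stake is how a result on the primary will be read. The Statistical Analyses section makes a phase 2 trial depend partly on there being no increase in adverse reactions under GTN. If a non-significant comparison of SBP below 110 mmHg were taken to meet that condition, the trial could pass with a sizeable excess of low SBP.

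**Working it through.** **Inputs from the article.** Difference 10 mmHg, SD 10 mmHg, 16 per group, 20% losses, 40 in total at 1:1 (Estimation of Sample Size; Randomization and Blindness); significance at p < 0.05 (Statistical Analyses); event = 24-hour average SBP below 110 mmHg (Primary Outcomes); entry SBP at least 120 mmHg (inclusion criteria). Sidedness is not stated.

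**1. Reproduce the plan's figure.** Normal approximation: n per group = 2 × (z_alpha + z_power)² × (SD/difference)².
- Two-sided alpha 0.05, power 0.80: 2 × (1.960 + 0.842)² × (10/10)² = 15.7, so 16. This matches.
- One-sided alpha 0.05, power 0.80: 2 × (1.645 + 0.842)² = 12.4, so 13. No match.
- Beta 0.8 taken literally (power 0.20), two-sided alpha 0.05: 2 × (1.960 − 0.842)² = 2.5, so 3. No match.
- Allowance for losses: 16/0.8 = 20 per group, 40 in total. This matches.

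The arithmetic is sound for mean SBP, and the intended terms are two-sided alpha 0.05 and power 0.80. An exact t-test gives 78% power at 16 and 87% at 20 per arm, an immaterial difference from the plan.

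**2. Carry the same assumptions to the binary primary.** Take 24-hour average SBP as normal with SD 10, control mean m and GTN mean m − 10. Then:
- control rate = Φ((110 − m)/10)
- GTN rate = Φ((120 − m)/10)

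Power is the sum, over all pairs of event counts in 20 and 20, of the two binomial probabilities wherever the two-sided test gives p < 0.05. The control mean is not in the article, so it is varied:

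| Assumed control arm | Control vs GTN rate | Fisher | Chi-square (uncorrected) |
|---|---|---|---|
| Mean 112 (maximum over 100–149) | 42.1% vs 78.8% | 56% | 68% |
| 10% below 110 (mean 122.8) | 10% vs 38.9% | 46% | 60% |
| Mean 130 | 2.3% vs 15.9% | 14% | 27% |
| Mean 140 | 0.13% vs 2.3% | below 0.1% | 0.1% |

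No control mean from 100 to 149 mmHg reaches 80%. With 16 evaluable per arm, the 10% row falls to 34% (Fisher) and 52% (chi-square).

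**3. What a non-significant result can hide.** By Fisher's test at 20 per arm, 4/20 vs 0/20 gives p = 0.11 and 5/20 vs 0/20 gives p = 0.047. For 4 vs 0, the uncorrected chi-square statistic is 0.2²/(0.1 × 0.9 × 2/20) = 4.44, p = 0.035. However, the expected count of events is only 2 per arm, a setting in which the exact test is the usual choice.

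**4. Precision available for the primary.** With 0 events in n patients, the one-sided 95% upper limit is 1 − 0.05^(1/n): 13.9% for n = 20 and 17.1% for n = 16.

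**The case against.** This is a phase 1, single-center pilot. The sample size also rests on published pilot-size recommendations, which can justify 40 patients without any power calculation. The section says openly that its calculation is for a difference in blood pressure and never claims 80% power for SBP below 110 mmHg. The binary outcome is a cut of the same average SBP, so the sizing variable is related to it. The article acknowledges its small sample, and the trial is meant to feed a later power calculation. All of this stands. It is why the number of patients need not change and why the point is not graver. It does not make the 80% apply to the primary: dichotomising loses information, and step 2 of the working shows how much.

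A reader might go further in three ways that the documents do not support.
- **That power for the primary is close to zero.** This follows only if the control mean is about 140 mmHg or more with SD 10. The entry floor of 120 mmHg makes low event rates plausible, but the article gives no rate. Its one hint, the 10th percentile, read as a 10% control rate, gives 46% by Fisher and 60% by chi-square.
- **That an SD of 10 contradicts 110 mmHg being a 10th percentile.** The percentile is attributed to prior studies of blood pressure and outcome, and the 10 mmHg difference to a different prior study. Nothing says that the SD describes the population behind the percentile.
- **That the analysis section leaves no test for SBP.** It introduces NIHSS and infarct volume as included among the continuous variables, not as the full list. The fair point is only that mean SBP is not declared as an outcome.

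Nor does the article say that non-significance will count as safe. Its condition for phase 2 is no increase in adverse reactions, without a stated criterion.

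**Conclusion.** The point holds in this form. The stated 16 per group is correct arithmetic for mean SBP, an undeclared outcome, under two-sided alpha 0.05 and 80% power. The declared binary primary has no power or precision statement. Under the plan's own shift and SD, its power at 20 per arm is below 80% throughout the range examined, with a maximum of about 56% (Fisher) or 68% (chi-square). Where it lies below that depends on the control rate, which is not given. These figures assume normally distributed 24-hour averages, equal SD in both arms and all 20 per arm evaluable. The mislabelling of alpha and beta needs no assumption. Severity: should be fixed. It affects what the trial can claim, not whether it can be run with 40 patients.

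**What to change.** Keep 40 patients and revise the sample-size paragraph and the outcome list:

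1. Replace the error terms with two-sided alpha 0.05 and power 0.80 (beta 0.20).
2. State that the 80% power is for a 10 mmHg difference in mean SBP with SD 10, and that it does not apply to the primary outcome.
3. Declare mean SBP over the first 24 hours as an outcome. The scheduled readings already supply it.
4. For the primary, state precision instead of power: 0 events in 20 GTN patients excludes a true rate above 13.9% (one-sided 95%), or above 17.1% if 16 are evaluable after the planned 20% loss.
5. Add that a non-significant difference in SBP below 110 mmHg will not be taken as evidence of safety.

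The cost is rewording and one added outcome, with no extra patients or measurements. The downside is that the stated figure for the primary becomes less favourable.
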